### Management

#### Study management

The study is overseen by a seven-person multidisciplinary management panel who meet to discuss progress and any issues that may arise. This includes input from medical, psychological, statistical, and physiotherapy backgrounds. In addition, this panel includes a stroke survivor who has been involved with the study from its conception. This includes the study design as well as the development of study documents, ensuring both are accessible and acceptable to the target population.

#### Data management

Where possible data entry will be electronic via electronic devices. This will occur through the programme ‘RedCap’. All data transfer and storage will be in line with the Data Protection Act (1998). Data entered manually will be subject to a yearly audit by the trial manager (data checking against raw scores). Identifiable information collected manually will be stored securely and kept for 10 years by University College London. A collection log will be in place to ensure all data is accounted for, and to act as a prompt for follow-up data collection. All study data will be stored and analysed in the UK.

### Evaluation

#### Outcome measures

As this is a feasibility study, no primary outcome was identified in accordance with guidelines [19]. Four quantitative measures and two qualitative processes will be used in this study as detailed below.

#### Interviews

It is vital that any complex intervention is acceptable to the target population [19]. Question 5 (how acceptable to stroke survivors is it to deliver Bridges in a group setting?) will be answered through interviews conducted with stroke survivors who have attended the group self-management intervention. Purposeful sampling will enable a range of demographics to be included. A sample size is not specified as, in keeping with guidelines for qualitative research, the process of recruitment and analysis are iterative, continuing until no new themes emerge from the data. Semi-structured interviews will be conducted as they allow flexibility in the ordering of questions and are widely used in health research [31]. All interviews will be conducted post intervention by a researcher who has not been involved with the project beforehand to minimise potential observer effects. The interviews will take place where the stroke survivor feels most comfortable; it is thought the majority of interviews will be in their own homes. The benefit of this is that being non-clinical, it may emphasise that the interviews had no impact on clinical care and again encourage more honest answers. Participants will have the option to bring a friend or family member with them. Each interview will be recorded using a dictaphone.

The topic guide has been developed by two researchers (EC and FJ). The topic guide was developed drawing on guidelines for interviews in health research to answer key questions relevant to the feasibility of the intervention [32]. The topic guide comprises four parts: (1) learning about the individual’s stroke journey, (2) experiences of taking part in the group self-management intervention, (3) life after the group self-management intervention and (4) questions about the research methodology (see Additional file 1).

#### Focus group

Question 6 (how acceptable is it to family/friends/carers to deliver Bridges in a group setting?) will be explored using focus groups. An individual’s social support can influence their likelihood to engage in new behaviours [30]. It is therefore important to understand the experiences of the friends, family and carers that attended the group self-management interventions as they are likely to be part of the self-management journey. A maximum of 12 family/friends/carers will be recruited to take part in up to two post intervention focus group/s, each with four to eight participants in. This is a balance between giving each member the space to voice opinion and ensuring enough data is captured [33]. Family/friends/carers who attended the group self-management intervention will be invited to a focus group to give feedback on the intervention. Focus groups have numerous advantages including stimulating discussion [33] and the ability to probe for more detail when potentially interesting topics arise [34].

Focus groups will take place in a non-clinical venue as this will minimise the possibility that individuals feel that what they say may impact their clinical support. Each focus group will last around 60 min and be audio recorded. The room will be set up in accordance with published recommendations, for example, a round table setting conducive to discussion [33]. The topic guide will be divided up into three parts: Firstly, attendees will be asked about their experiences of the group in general; secondly, about limitations, challenges and possible benefits, as well as what they may have learnt from the group and in turn what they feel the person they attended with may have learnt from the group. The discussion will end with questions asking about future possibilities for group self-management interventions and exploring whether the intervention has any longevity. The questions that will be asked during each focus group were developed with a stakeholder group using questions that utilise everyday language. For example, do you feel confident that you and the stroke survivor you attended with can carry on under your own steam? (see Additional file 2).

#### Quantitative outcome measures

Question 7 (what is the magnitude and variability of change in outcome measures post intervention?) will be answered using quantitate outcome measures. MRC guidelines that state identifying a single primary outcome in complex interventions may not make the best use of data [23]. Identifying a range of measures (both qualitative and quantitative) will maximise the chance that unexpected consequences can be captured.

The Stroke and aphasia quality of life measure-39 (SAQOL) uses a 39 item scale which is split into four subdomains (physical, psychosocial, communication and energy) to assess quality of life [35]. The Stroke self-efficacy scale (SSES) gives an indication of an individual’s belief in their own ability to complete certain tasks [36]. The Nottingham extended activities of daily living scale (NEADLS) will be used to get insight into the day-to-day functioning of each individual [37]. The Hospital Anxiety and Depression Scale (HADS) will give insight into an individual’s mood [38]. Participants are given the option to complete questionnaires over the phone or in person with a member of the research team. If posted participants are called to confirm if they have received the questions and to see if they require any assistance.

### Analysis

Analysis of data will be completed by the research team which includes a statistician and an expert in qualitative research. Due to the nature of the intervention and extended follow-up periods for the intervention group, it is not possible to blind participants or those analysing data to the condition. If missing data occur, we will describe their numerical impact on the actual sample observed as well as the possible reasons for dropout, which we aim to collect as carefully as possible. Given the nature of the study and the limited sample size, we do not plan on doing formal and complex modelling (e.g. multiple imputation). However, we will assess the impact of possible missingness mechanisms on the results of the data analysis.

#### Questions 1–4

Questions 1 to 4 (1. How many stroke survivors are eligible and how quickly can they be recruited? 2. What will the level of adherence and attendance be? 3. What will follow-up response rates to questionnaires be? 4. Are participants willing to be randomised to a waitlist control in a group self-management study?) will be answered using frequency counts and descriptive statistics. Session attendance will be monitored to provide dropout and partial-completion rates. Those who do not complete the intervention will be asked why and the answers categorised to determine the most common reasons. To gain insight into recruitment, the proportion of stroke survivors who met the eligibility criteria will be documented as well as how many were approached to take part and the length of time taken to recruit all 60. Willingness of participants to be randomised will be assessed using the number declining to participate as a result of randomisation will be documented. To assess follow-up rates, the date which questionnaires are sent out and the date returned will be recorded to give an average response time. The number of non-returns will also be documented.

#### Question 5 and 6

Questions 5 (how acceptable to stroke survivors is it to deliver Bridges in a group setting?) and 6 (how acceptable is it to family/friends/carers to deliver Bridges in a group setting?) will be answered using qualitative interviews (stroke participants) and focus groups (family and friends). Interviews will be transcribed and analysed by two researchers using inductive thematic analysis. Inductive thematic analysis is recommended for preliminary health service research and when key themes reflecting variations in the data need to be identified as with this project [29, 30]. Codes will be created using phrases or words drawn directly from the data. These will then be grouped to develop categories and themes. Both researchers will write a summary of their interpretations and discuss them together, including codes and their descriptive groupings. Any disagreement will be discussed by the researchers and at subsequent management meetings if further resolution is needed. Thematic analysis will then involve iteratively exploring which themes are identified across the data set. The data set will then be re-read to find illustrative examples of themes and adjusting them to reflect any new data gathered [39]. Data will be managed using Nvivo 10.

#### Question 7

Question 7 (What is the magnitude and variability of change in outcome measures post intervention?) will be answered using an analysis of covariance (ANCOVA). In line with guidelines [19], there is no formal power calculation for the study, meaning results are not statistically powered to find an effect. Therefore, results are to be considered only as preliminary. An ANCOVA will analyse the results comparing pre-post intervention scores (within subjects) and the intervention to the waitlist group (between subjects). Demographics will be included as co-variates where appropriate, for example living situation and time post stroke. Variability in outcome measures will provide the information needed to calculate the power for future research on this topic.

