#### Stroke survivors

Recruitment will be overseen by a Clinical Research Network. The setting will be a Hyper Acute Stroke Unit (HASU) in a central London Hospital. The intense nature of HASU means patients are initially consented to a Permission To Contact register (PTC) and given information about the study, allowing individuals to read the information sheet in their own time. The PTC is a list of those who have given permission to be contacted by researchers in the future. It enables access to a naturally occurring sample within the stroke population which minimises the risk of selection bias and maximises the chance the sample is representative of the target population. The PTC has been recruiting stroke survivors since 2013. As a result, it contains individuals who had their stroke up to 2 years previously, offering a greater range of time post stroke than if recruiting from the start of this research. A limitation of the PTC used for the proposed study is that it only comprises patients who can consent for themselves during their stay in HASU so may result in a sample of individuals with less severe strokes. This will be acknowledged in the final analysis and write up of findings.

After December 2015, the PTC was adapted to become the PTC+ which does include patients that are unable to consent for themselves (a family of friend can consent on their behalf). This could minimise a possible selection bias towards participants with less severe strokes. To gain the benefits of both these registers, we will recruit from the PTC for the first 15 participants and the PTC+ for the remaining 45. Recruitment will start from the first entry on each register and continued in chronological order. A member of the research team will enrol participants in the study (including consent). Once an individual has been enrolled by a member of the research team, they will be randomly allocated to a condition by a statistician using blocked randomisation to ensure balanced numbers. The first patient was enrolled on 25/02/2016. Question 1 (how many stroke survivors are eligible for the group self-management intervention and how quickly can they be recruited?) will be answered through documentation of this recruitment process.

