Once completed, this research will determine if the intervention should progress to a full RCT. It will do so by exploring the acceptability of the intervention, the occurrence of serious adverse events occur, the appropriateness of research measures and adherence rates which should be over 85%. It will also inform the design of future work assessing the efficacy of a group self-management intervention. It will do so in a number of ways. Firstly, this research will help determine the project timeline as information about the number and rate of eligible participants that can be recruited as well as the follow-up questionnaire return rate will be available. Secondly, it will determine whether future work should randomise participants to a condition as their willingness to do so will be documented. Thirdly, the design of the group self-management intervention may be adapted based on the acceptability to stroke survivors and family/friends/carers. Finally, the information to conduct a power calculation which will determine the sample size of a larger trial will be available as a result of documented dropout rates and standard deviation of outcome measures.

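### Recruitment speed is read from the time to enrol all 60, which pools stored register entries, new patients and team capacity, so the rate passed to the main trial may overstate sustainable accrual

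*Protocol article*

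**What the plan says.** The Analysis section of the protocol article (Questions 1–4) says how Question 1 will be answered. Two items give denominators: "the proportion of stroke survivors who met the eligibility criteria will be documented", and the number approached. The speed item is a calendar time; the text asks for "how many were approached to take part and the length of time taken to recruit all 60".

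The Discussion gives the result a use: "this research will help determine the project timeline as information about the number and rate of eligible participants that can be recruited".

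The Recruitment section (Stroke survivors) describes the source of participants. On the older register: "The PTC has been recruiting stroke survivors since 2013". After December 2015 it was adapted into the PTC+, which also admits patients who cannot consent for themselves. On the split: "we will recruit from the PTC for the first 15 participants and the PTC+ for the remaining 45". On the order of approach: "Recruitment will start from the first entry on each register and continued in chronological order". First enrolment was on 25/02/2016. The authors chose stored entries deliberately, because the PTC has the merit of "offering a greater range of time post stroke than if recruiting from the start of this research".

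The stated limitations cover stroke severity, the single hospital and the difficulty of standardising the intervention. None concerns the effect of stored entries on the recruitment rate.

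**The concern.** A recruitment rate used to plan a later trial should say how many participants a site can supply per month and keep supplying. Dividing 60 by elapsed time gives that only if patients become available during the time counted. Here the 15 PTC participants count in the numerator, while the months in which they accumulated on the register fall outside the denominator. The PTC+ had a short head start as well, and it could build up entries while the PTC was being worked.

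Elapsed time also depends on how fast the team can approach people and fill groups of five to eight. The pooled rate therefore has at least three components (stock, inflow and capacity), and the stated measure does not separate them. The two registers also differ in consent rules, so they may differ in yield.

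If the pooled rate is taken as patient supply, the main trial's timeline or number of sites could be set wrongly. The more natural risk is a timeline that is too short. Recruitment speed is one of the study's own named feasibility questions.

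**Working it through.** **Inputs from the article.** Total 60; 15 from the PTC and 45 from the PTC+; PTC recruiting since 2013; PTC+ after December 2015; first enrolment 25/02/2016; eligibility requires discharge from community rehabilitation. The article gives no recruitment period, register size or monthly inflow.

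**Step 1: the plan's own figure.** 50 + 10 dropouts = 60, and 15 + 45 = 60. Both agree. No recruitment rate is stated, so there is none to reproduce.

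**Step 2: shares and age of each source.**
- PTC: 15/60 = 25%. From 1 January 2013 to 25/02/2016 is 37.8 months; from 31 December 2013 it is 25.8 months. The register was therefore about 26 to 38 months old at first enrolment.
- PTC+: 45/60 = 75%. From 1 December 2015 to first enrolment is 2.8 months; from 31 December 2015 it is 1.8 months. A later opening would make this shorter.

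**Step 3: simplest case.** Suppose new patients arrive on the PTC+ at L recruitable per month, inflow is the only limit, and the 15 stored patients add no time. Then T = 45/L, and the observed rate is 60/T = (60/45) × L = 1.33 × L. This is before any PTC+ head start.

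**Step 4: allowing for head start, waiting and capacity.** Let lead be the PTC+ head start (1.8 to 2.8 months, from Step 2). Let lag be the wait until rehabilitation discharge and C the most participants the team can enrol per month. L, lag and C are assumptions.

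T = max(60/C, 45/L + lag − lead); observed rate = 60/T; ratio = observed rate / L.

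| Assumed L, lag, C | T (months) | Observed rate per month | Ratio to L |
|---|---|---|---|
| 3 per month, 0, C at least 6 | 12.2 to 13.2 | 4.6 to 4.9 | 1.5 to 1.6 |
| 3 per month, 6 months, C at least 6 | 18.2 to 19.2 | 3.1 to 3.3 | 1.04 to 1.10 |
| 5 per month, 6 months, C at least 6 | 12.2 to 13.2 | 4.6 to 4.9 | 0.91 to 0.99 |
| 5 per month, any lag from 0 to 6, C = 4 | 15.0 | 4.0 | 0.80 |

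For the first row with the longer head start: 45/3 + 0 − 2.83 = 12.2 months; 60/12.2 = 4.9 per month; 4.9/3 = 1.6.

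Over the whole assumed grid (L from 2 to 8 per month, lag from 0 to 6 months, C from 4 per month to unlimited) the ratio runs from 0.5 to 2.7. The low end is L = 8 with C = 4 (4/8 = 0.5). The high end is L = 8 with no lag, no capacity limit and the longer head start (T = 45/8 − 2.83 = 2.8 months; 60/2.8 = 21.5 per month; 21.5/8 = 2.7).

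**Reading.** The same elapsed time can arise from quite different inflows: the first and third rows give the same T and the same observed rate from 3 and from 5 new patients per month. The stated speed measure therefore does not identify patient supply.

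**The case against.** The best defence is that most of the sample does not come from an old backlog. The PTC+ supplies 75% and was at most about 2 to 3 months old at first enrolment. Its earliest entries may not yet have been discharged from rehabilitation. For those 45, elapsed time may largely reflect new entries, which is the quantity wanted. This stands, and it limits the backlog argument to the 15 PTC patients plus whatever accumulated on the PTC+ meanwhile.

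Second, the direction of bias is not shown. With a capacity limit or a long wait for discharge, the observed rate can fall below inflow. This also stands. It does not rescue the measure, because a figure that could err either way by an unknown amount is a weak basis for a timeline.

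Third, the plan also records the proportion eligible and the number approached, and says only that the information will help with the timeline. These counts are useful, but as stated they are not tied to the months over which the entries accrued.

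Fourth, a breakdown by register might be left to a fuller document. The point here does not rest on a missing table: the article itself names the speed measure and its use, and the measure does not isolate patient supply.

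Finally, a later trial might also recruit from registers, so part of the rate could carry over. The article does not say how it would recruit, only that it should use more than one site.

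**Conclusion.** The point holds in a limited form. Time to enrol 60 pools stored entries, new inflow and team capacity, and the article passes the rate on without a caveat. It may overstate sustainable accrual. The one figure that follows directly from the stated split is 60/45 = 1.33-fold, and it assumes that inflow is the limit, that the 15 stored patients add no time and that the PTC+ has no head start. Under wider assumptions the ratio lies anywhere from 0.5 to 2.7.

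A reader might infer more, and the documents do not support it:
- That the whole sample comes from a filled register. This clearly fits only the 15 PTC participants.
- That the rate is certainly too high. No inflow, register size or recruitment period is given, so the sign is open.
- That the overstatement is several-fold. Assuming that the 15 were enrolled in 3 months from entries spanning 6, 12 or 24 months gives 5.0 per month against 2.5, 1.25 or 0.63, which is 2-, 4- or 8-fold. Those spans are invented and describe a quarter of the sample, not the pooled measure.
- That the register will be used up before a main trial. The article does not say so.

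The change is worth making because it alters the figure handed to the main trial. It does not threaten the conduct of this study.

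**What to change.** For Question 1, tabulate the PTC and the PTC+ separately: entries reached, eligible, approached and enrolled, each with the months of register entry spanned (first to last entry reached). Use register-entry dates; date of stroke is collected at baseline for participants only. Working each register in date order implies that entry dates are available.

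Base the main trial's timeline mainly on the PTC+ yield per site-month. Report the PTC yield beside it, noting that loss of contact among older entries may lower it, so that it could understate current supply. Keep the time to enrol all 60 as a measure of workload, labelled as drawn partly from stored entries.

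Design, sample size and conduct are unchanged. The cost is a little more tabulation and a stated recruitment rate that may look less favourable.

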### Dissemination

All co-applicants will facilitate dissemination to a range of sources including academics, stroke survivors and the relevant funders, e.g. National Institute for Health Research—Research for patient benefit. If feasible, dissemination will include progression to the subsequent randomised control trial. In addition, dissemination will include a mixture of presentations, publications and web-based social media (e.g. twitter).

## Discussion

Interest is growing in group self-management interventions as they may facilitate the long-term management of stroke, an area which is currently understudied. However, before group self-management interventions can be evaluated as part of a fully powered trial, the feasibility of such interventions need to be assessed. This protocol detailed the methodology and methods that will be used for a funded exploration into whether it is feasible to deliver an existing self-management intervention (Bridges) in a group setting.

When designing the study, care was taken to use methodology and methods advocated by current research guidelines. This includes the Medical Research Guidelines for complex interventions [21], TiDieR guidelines for intervention descriptions [22], SPIRIT reporting guidelines [20], and NIHR advice on feasibility studies [19]. The study also has a multidisciplinary management panel who co-designed the methodology, including a stroke survivor. However, there are some limitations of the proposed study that should be addressed. The recruitment strategy means that participants will be recruited from one hospital which limits the geographical reach. Although it was decided that this was acceptable for the current study as the priority is to assess feasibility, a larger future trial should include more than one recruitment site to increase the generalisability of the data. In addition, as stated in MRC guidelines, it can be problematic for complex interventions to be fully standardised, especially as group self-management interventions should retain enough flexibility to adapt to context and ensure they are tailored to each individual [11]. This makes replicability and fidelity to protocol harder to asses. To overcome this, the TiDieR guidelines were used which provide a reporting procedure for interventions that is flexible enough to incorporate adaptions to context [22].

Once completed, this research will determine if the intervention should progress to a full RCT. It will do so by exploring the acceptability of the intervention, the occurrence of serious adverse events occur, the appropriateness of research measures and adherence rates which should be over 85%. It will also inform the design of future work assessing the efficacy of a group self-management intervention. It will do so in a number of ways. Firstly, this research will help determine the project timeline as information about the number and rate of eligible participants that can be recruited as well as the follow-up questionnaire return rate will be available. Secondly, it will determine whether future work should randomise participants to a condition as their willingness to do so will be documented. Thirdly, the design of the group self-management intervention may be adapted based on the acceptability to stroke survivors and family/friends/carers. Finally, the information to conduct a power calculation which will determine the sample size of a larger trial will be available as a result of documented dropout rates and standard deviation of outcome measures.

